Early separation from the premature infant also has negative impacts on parents and their parenting. Parents of preterm infants have reported feelings of separation when their infant is admitted to an NICU. Separation makes parents feel insufficient, unnecessary, and as if they are not part of the infant's care team. A prolonged early separation may also lead to parental depression. Specifically, parents of prematurely born infants are at higher risk of postpartum depression (PPD), with rates varying from 6 to 48 percent. The depression scores of some parents remain high (17–20%) until the second year after the preterm delivery. Depression has typically a strong comorbidity with anxiety. Although, anxiety is a separate mood disorder having a different symptomatology than depression. NICU parents have also an elevated risk for anxiety symptoms with rates varying from 18 to 72 percent.

The problems mentioned above are well recognized by neonatal professionals, and thus family-centered care (FCC), is strongly advocated and considered as “state of the art” in modern neonatal intensive care. FCC has been shown to improve neonatal, parental, and health service outcomes. However, there is no consensus regarding FCC practices, leading to confusion in its implementation. Developmental psychology theories (DPT) are grounded on strong empirical research and are better operationalized than FCC, and thus they can guide the content of interventions and implementation as well as the choice of outcomes when evaluating the effectiveness of FCC.

We have developed an educational intervention that is based on knowledge from DPTs, the nursing sciences, and evidence-based medicine. The intervention, called “Close Collaboration with Parents” is targeted at hospital nursing and medical staff to improve their skills to support the early parent–infant relationship. By educating the whole staff of a unit, we can make the benefits available for all patient care in the unit. The innovation of the intervention is related to its multiprofessional approach and the use of experiential learning with a mentor as a facilitation method. We have implemented and studied the intervention in 12 hospitals in Finland between the years 2009 and 2020. Our research shows that the Close Collaboration with Parents training improves units’ FCC practices, increases parents’ presence during hospital care by 37%, increases parents’ skin-to-skin care by 50%, and decreases the percentage of mothers who scored over the probable clinical depression cutoff from 10% to 2%. Staff have reported that the training helped them to change their attitudes and trust parents as caretakers.

Close Collaboration with Parents is a complex intervention because it aims to improve the care model of the unit. To fully understand the functioning of a complex intervention, a systematic approach is recommended for conducting process evaluations and identifying key impact mechanisms. However, there are no previous studies about the impact mechanisms of FCC interventions to explain how the interventions produce positive changes in parental outcomes.

## **Research Objectives and Methods**

The overall goal is to address the knowledge gap related to the impact mechanisms of FCC interventions on improvements in patient outcomes. The specific goal is to test a potential impact mechanisms model of the Close Collaboration with Parents intervention (Figure 1).

### Process evaluation to test the impact mechanisms

[figure not shown]

**Figure 1.** Process evaluation is used as a theoretical framework to construct a logical model to explain the change mechanisms of Close Collaboration with Parents.

#### The specific research questions are as follows:

1. What is the achieved level of fidelity in the implementation process of the intervention in the Estonian context?
2. Does the intervention promote immediate changes in the staff's collaboration competence, perception of the FCC care provision, and reflective thinking?
3. Does the intervention have a significant positive effect on the FCC practices of the units?
4. Does the intervention have a significant positive effect on parenting self-efficacy, parental mood and parents' readiness for discharge at the time of hospital discharge?
5. If the answers to questions 2, 3, and 4 are positive, we will then seek to answer whether the potential impact mechanisms mediate the improvements in unit FCC practices, parental self-efficacy, mood and readiness for discharge.

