## Materials and Methods

### Design

A quasi-experimental before and after intervention design is used to test the effect of the intervention, where the impact mechanisms are treated as mediators of the change.

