### Sample

The subjects are employees of five neonatal units of three Estonian hospitals participating in the Close Collaboration with Parents intervention (hereinafter: staff) and newborns cared for in the units and their parents (hereinafter: families). Three of the units are at Tallinn: West-Tallinn Maternity Hospital (NICU and neonatal unit), the Department of Anesthesiology and Intensive Care (PICU/level IIIB) and the Department of Neonatal and Infant Medicine (NICU/level II) at the Children’s Hospital. The Department of Anesthesiology and Intensive Care is an open-bay intensive care unit, while the Department of Neonatal and Infant Medicine is a single-family-room unit. Another two units are located in Tartu University Hospital: the Department of Neonatal and Pediatric Intensive Care (PNICU, level IIIC) and a stepdown unit (level II). PNICU is an open-bay unit while the stepdown unit has two open-bay intensive care rooms (mothers have their bed in another room of the ward) and 8 single-family rooms.

The inclusion criteria for the families are: 1) families whose newborns have been hospitalized during the first 28 days of infant life, 2) expected length of stay of the newborn is at least three days, 3) discharge is planned to happen within a week, and 4) at least one parent has agreed to participate in the study. The staff working in the units during the entire study period is eligible for the study.

Families are recruited during a four-month period before and after the intervention, with the aim to recruit at least 50 families per participating hospital in both periods. Some newborns may be treated in a different hospital or in different units of the same hospital. In the case of a transfer, the family is asked to fill in only the Family Center questionnaire (Appendix 10) if the newborn has been in that unit for more than 72 hours.

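### Question 5 permits the mediation analysis only after positive answers to questions 2, 3 and 4, so the study's specific goal can go untested although a mechanism operates

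*Protocol*

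**What the plan says.** Under Research Objectives and Methods the protocol states: "The specific goal is to test a potential impact mechanisms model of the Close Collaboration with Parents intervention". The Design section describes a before-and-after comparison "where the impact mechanisms are treated as mediators of the change", with no condition attached.

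The list of research questions adds one. Question 5 reads: "If the answers to questions 2, 3, and 4 are positive, we will then seek to answer whether the potential impact mechanisms mediate". The changes to be explained there are those in family-centred care (FCC) at unit level and in the parent outcomes. The three questions it depends on are:

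- Question 2 (staff): "Does the intervention promote immediate changes in the staff's collaboration competence, perception of the FCC care provision, and reflective thinking"?
- Question 3 (units): "Does the intervention have a significant positive effect on the FCC practices of the units"?
- Question 4 (parents): "Does the intervention have a significant positive effect on parenting self-efficacy, parental mood and parents' readiness for discharge at the time of hospital discharge"?

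The three are joined by 'and'. The protocol does not say what happens to the mechanism model if one answer is negative. It also does not say whether one construct or every construct must be positive for question 2 or question 4 to count as positive.

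**The concern.** Two parts of the protocol pull against each other. The goal and the design treat mediation as what the study is for. Question 5 treats it as a follow-up that is carried out only if three earlier results come out well.

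The condition is also statistically unsound where it asks for significant total effects. With one pathway and no direct effect, the total effect is the product of the path from intervention to mediator (a) and the path from mediator to outcome (b). On a standardised scale with both paths below 1, that product is smaller than either path and harder to detect. A direct effect in the opposite direction can hide it further. A non-significant total therefore does not show that the mechanism is absent.

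Two things are at stake. The study may end without an answer to its own goal, although the data to address it were collected. And any indirect effects that are reported will have been selected on large observed totals, which inflates them.

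**Working it through.** **Inputs from the protocol.** The Sample section gives "The subjects are employees of five neonatal units of three Estonian hospitals" and a recruitment target "with the aim to recruit at least 50 families per participating hospital in both periods". Hence 3 × 50 = 150 families per period, and 5 units × 2 periods = 10 unit-period cells. The protocol gives no power, alpha, effect size or intracluster correlation, so there is no figure of its own to reproduce.

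**Assumptions.** Two-sided alpha 0.05; mediator and outcome with within-period SD 1 (outcome when there is no direct effect); mediator measured on each family, for example parent-rated FCC; no clustering; no direct effect unless stated; a = b = 0.3 to 0.5.

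**Step 1: power for the total effect and for the two paths.**

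The standard error of a between-period difference is √(2/150) = 0.1155. Power is approximately Φ(effect/SE − 1.96). The SE of b is about √((1 − b²)/300).

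| a = b | Total a × b | Power, total | Power, a | b / SE(b) |
|---|---|---|---|---|
| 0.3 | 0.09 | Φ(0.78 − 1.96) = 0.12 | Φ(2.60 − 1.96) = 0.74 | 0.3/0.0551 = 5.4 |
| 0.4 | 0.16 | Φ(1.39 − 1.96) = 0.28 | Φ(3.46 − 1.96) = 0.93 | 0.4/0.0529 = 7.6 |
| 0.5 | 0.25 | Φ(2.17 − 1.96) = 0.58 | Φ(4.33 − 1.96) = 0.99 | 0.5/0.0500 = 10.0 |

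The b path is detected almost always, so the joint test (both paths significant) has roughly the power of the a path. Simulation agrees: the total is significant in about 11-58% of studies and the joint test in 73-99%. At a = b = 0.4, about 66% of simulated studies have significant paths but a non-significant total.

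The result is sensitive to a direct effect. At a = b = 0.4 with a direct effect of +0.1, the total is 0.26 and its power Φ(2.25 − 1.96) = 0.61. At a = 0.5, b = 0.4 with a direct effect of −0.2 (unit residual variance), simulation gives 3% for the total and 99.5% for the joint test.

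**Step 2: chance that all three conditions are met when every effect is real.**

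- Independent, 80% power each: 0.8³ = 0.51. Correlation 0.3 to 0.7 (simulated): 0.57 to 0.66.
- Independent, 90% power each: 0.9³ = 0.73. Correlation 0.3 to 0.7: 0.76 to 0.81.

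Mediation then goes unasked in 1 − 0.81 = 19% to 1 − 0.51 = 49% of such studies.

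**Step 3: selection bias.** At a = b = 0.4, the mean estimated indirect effect among simulated studies with a significant total is about 0.18 against a true 0.16, an excess of about 12%. Over equal paths of 0.3 to 0.5 the excess is about 7-20%, largest for the weakest paths. The total effect shown beside it is inflated more: 0.298 against 0.160 at a = b = 0.4. A proportion mediated would be distorted accordingly.

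**Step 4: does this apply to staff mediators?** No. The protocol describes no link between a staff member's scores and individual families, so the apparent link is unit and period, that is 10 cells. Simulations of that structure (mediator shift 0.4, slope 0.4, assumed cell-level variation) gave joint power of about 4-15%.

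**The case against.** The best defence is that the aim presupposes improvement. The overall goal concerns mechanisms acting on improvements in patient outcomes, and question 5 asks what mediates the improvements. Showing a change before explaining it is a recognised sequence. Questions 1-4 also examine links of the model in their own right: fidelity, staff change, unit practice and parent outcomes. This explains why the condition was written. It does not make a significant total a valid test of whether a mechanism operates, and it does not supply a fallback.

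Three further objections limit the size of the point, and they stand.

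- **Question 2 is different.** Change in the staff measures is the a path, so asking for it is the least objectionable part. The harm comes from requiring significant totals in questions 3 and 4, and from requiring everything together.
- **The assumed total effect may be pessimistic.** Paths of 0.4 × 0.4 imply only 0.16 SD. The protocol's background cites a fall in probable maternal depression from 10% to 2%. At 150 mothers per period, ignoring clustering, power for that difference is about 83%.
- **The individual-level illustration may not be the main pathway.** Question 5 lists unit FCC practices among the improvements to be explained, which leaves the staff measures as the evident mediators. Step 4 shows that the favourable joint-test figures do not transfer to them.

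A reader might infer that the rule blocks the main question in most studies where the mechanism is real. The documents do not support that: the three-condition range is 19-49%, and the larger figures need weak paths and no direct effect. A reader might also take all eight scales as having to be positive, which gives 0.8⁸ = 17% if independent. The protocol never states that reading, and outcomes reported by the same parents are unlikely to be independent.

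**Conclusion.** The point holds as a defect of wording with analytic consequences. Question 5 makes the specific goal depend jointly on three earlier positive answers, two of them framed as significant effects, with no fallback and with 'positive' undefined for questions that cover several constructs. That condition is not needed for an indirect effect and biases the indirect effects that are reported.

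It is not simply a detail left to an analysis plan. The protocol itself fixes whether mediation is examined at all, and a plan that follows it inherits the rule.

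Every magnitude rests on effect sizes, power and correlations that the protocol does not state, and the path simulation also ignores clustering. It should not be inferred that dropping the condition makes mediation well powered here: clustering lowers power for total and indirect effects alike, and for staff mediators linked only through five units and two periods power is low either way. The point should be fixed, but it does not threaten the data collection or the answers to questions 1-4.

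**What to change.** In question 5, remove positive results in questions 2-4 as a condition for doing the analysis. State that indirect effects with confidence intervals will be estimated for the mediator-outcome paths of the Figure 1 model whatever those results, and reported beside the corresponding total effects. Use the answers to questions 2-4, including whether the mediator changed, for interpretation only. For staff mediators, say that the estimates rest on unit-by-period contrasts and will be imprecise.

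The cost is a change of protocol wording and some extra analysis of data already planned for collection. The drawback is more estimates to report. Presenting them as intervals, not as separate significance claims, keeps that manageable.

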## Materials and Methods

### Design

A quasi-experimental before and after intervention design is used to test the effect of the intervention, where the impact mechanisms are treated as mediators of the change.

### Sample

The subjects are employees of five neonatal units of three Estonian hospitals participating in the Close Collaboration with Parents intervention (hereinafter: staff) and newborns cared for in the units and their parents (hereinafter: families). Three of the units are at Tallinn: West-Tallinn Maternity Hospital (NICU and neonatal unit), the Department of Anesthesiology and Intensive Care (PICU/level IIIB) and the Department of Neonatal and Infant Medicine (NICU/level II) at the Children’s Hospital. The Department of Anesthesiology and Intensive Care is an open-bay intensive care unit, while the Department of Neonatal and Infant Medicine is a single-family-room unit. Another two units are located in Tartu University Hospital: the Department of Neonatal and Pediatric Intensive Care (PNICU, level IIIC) and a stepdown unit (level II). PNICU is an open-bay unit while the stepdown unit has two open-bay intensive care rooms (mothers have their bed in another room of the ward) and 8 single-family rooms.

The inclusion criteria for the families are: 1) families whose newborns have been hospitalized during the first 28 days of infant life, 2) expected length of stay of the newborn is at least three days, 3) discharge is planned to happen within a week, and 4) at least one parent has agreed to participate in the study. The staff working in the units during the entire study period is eligible for the study.

Families are recruited during a four-month period before and after the intervention, with the aim to recruit at least 50 families per participating hospital in both periods. Some newborns may be treated in a different hospital or in different units of the same hospital. In the case of a transfer, the family is asked to fill in only the Family Center questionnaire (Appendix 10) if the newborn has been in that unit for more than 72 hours.

### Data collection

The pre-intervention data is collected in spring 2021 during a four-month period when the training on unit mentors is going on, but the implementation to the unit has not begun. The data measuring the fidelity of intervention implementation will be collected between January 2021 and October 2022. The post-intervention data is collected in the shift of the years 2022 and 23 during a four-month period. (Figure 2).

| Data collection                                                                                                | 2021       | 2022                    | 2023         |
|----------------------------------------------------------------------------------------------------------------|------------|-------------------------|--------------|
| Parents’ data:
FCC, parental self efficacy, parental depression and anxiety, and discharge readiness | 2-4/21     |                         | 11/22 – 2/23 |
| Staff’s data:
Collaboration competence, reflective thinking, provision of FCC                        | 2-4/21     | After training Phase II | 11/22 – 2/23 |
| Fidelity                                                                                                | 1/21-10/22 |                         |              |
| CC Intervention                                                                                         | 1/21-8/21  | 9/21-10/22              |              |

**Figure 2.** Illustrates the timeline of the data collection.

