#### *Collaboration competence questionnaire*

A questionnaire is used to assess the collaboration competence of the staff at the beginning of the intervention, in the middle of the implementation and in the end. The questionnaire is specifically created to assess competencies that are relevant for the Close Collaboration with Parents training program. The questionnaire includes 21 questions that are evaluated with scale from 1 to 10 (1=not competent at all, 10=extremely competent). If the question does not ably the daily work role of the professional option "Doesn't belong to my role" can be used. (Appendix 2)

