All the data will be handled anonymously. The participants will get an ID code that is used when data is stored and analyzed. The recruitment log of the parents and staff members are used to undo the ID codes and, therefore, they are kept separately from the data files. The analytic softwares (Google Analytics, Hotjar and Vimeo) also track anonymously participants' behavior on the e-learning module's website. The personal details (password, email, etc) are not recorded and the IP addresses are anonymized by cutting out the last few digits, so only the rough geographical area of access to the e-learning module is identified. The logs and all the data will be destroyed five years after the last publication from the data.

The intervention

The Close Collaboration with Parents intervention will be carried out in the four NICUs in Estonia. The delivery of the intervention follows a structure that has been developed and fine-tuned between 2009 and 2020 when it was implemented in 14 NICUs. First, experienced nurses or doctors from the units will undergo a three-week training to become "unit mentors," and then these unit mentors will train other members of staff. The training of the units is strongly based on experiential learning utilizing bedside practices, reflection of the practices, and application of this knowledge in everyday clinical situations. Theoretical teaching, which precedes clinical bedside mentoring, will occur through a new e-learning tool. Each staff member will spend about four working days training alongside his or her routine work. The unit mentors will function as facilitators for all the staff, and they have dedicated time for this. The content of the bedside practices is guided by a manual. To support the delivery of this phase, the training

team will provide frequent remote supervision for the unit mentors and leadership. The units have committed to allocate the resources for the implementation of the intervention. The applicant will have the main responsibility for the delivery of the training. The aim is to train about 75% of the staff members in the units during the 18-month period.

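### The staff pre-intervention wave overlaps the training of the unit mentors, who belong to the staff sample, so mentors are not guaranteed an untrained baseline

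*Protocol*

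**What the plan says.** The Data collection section places the pre-intervention wave in spring 2021: "The pre-intervention data is collected in spring 2021 during a four-month period when the training on unit mentors is going on". It adds the reason for treating this as a before period: "but the implementation to the unit has not begun". In Figure 2 the intervention has two blocks, 1/21-8/21 and 9/21-10/22. Staff data are collected in 2-4/21, again during the implementation, and in 11/22-2/23.

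The description of the intervention, which follows the Data management section, says who the mentors are and what they receive: "experienced nurses or doctors from the units will undergo a three-week training". Other staff members spend about four working days in training, and the mentors deliver it.

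The Sample section makes no exception for mentors: "The staff working in the units during the entire study period is eligible for the study". The daily web questions on family-centred care (FCC) provision go to all staff of the units. The section on the competence instrument ties the first measurement to the start of the intervention, not to a time before it: "A questionnaire is used to assess the collaboration competence of the staff at the beginning of the intervention". No earlier staff wave is described.

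**The concern.** Research question 2 asks whether collaboration competence, perceived FCC provision and reflective thinking change. The Design section and research question 5 then treat the impact mechanisms as mediators. The before value in these measures therefore has to be free of training.

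The protocol's safeguard is that implementation in the unit has not begun. That protects the scores of colleagues who have not yet been mentored. It does not protect the mentors' own scores, because their own training is part of the intervention and is meant to change what these instruments measure. A mentor who answers part-way through or after the three weeks gives a before value that already contains some of the effect. The change to both later staff waves then starts too high.

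**Working it through.** The plan states no figure on this point, so there is none to reproduce. The check has two parts.

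**1. Dates (Figure 2)**
- Staff baseline: February to April 2021, 3 months.
- First intervention block: January to August 2021, 8 months.
- Overlap: 3 of 3 baseline months. The block opens 1 month before the baseline and runs 4 months after it closes.
- The text speaks of four months of baseline collection and the figure shows three. The overlap does not depend on which is meant, because the text itself says that mentor training is under way.
- The three weeks are not dated within the block. For illustration only, if mentor training were spread evenly over the 8 months, the share completed would be 1/8 = 12.5% at the start of February, 2.5/8 = 31% by mid-March and 4/8 = 50% by the end of April.

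**2. Effect on the pooled staff change**

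Let p be the mentors' share of respondents, g their true gain relative to other staff (whose gain is set to 1), and e the share of that gain already reached when they give the baseline answer.

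- True mean change: (1 − p) + p·g
- Observed mean change: (1 − p) + p·g·(1 − e)
- Understatement: p·g·e / [(1 − p) + p·g], which reduces to p·e when g = 1

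The documents give none of the three. Assumed: p = 5% to 15%, g = 1 or 2, e = 0 to 100%.

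| p | g | e = 0 | e = 50% | e = 100% |
|---|---|---|---|---|
| 5% | 1 | 0 | 2.5% | 5% |
| 15% | 1 | 0 | 7.5% | 15% |
| 5% | 2 | 0 | 0.05/1.05 = 4.8% | 0.10/1.05 = 9.5% |
| 15% | 2 | 0 | 0.15/1.15 = 13.0% | 0.30/1.15 = 26.1% |

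With equal gain the result scales with p. A mentor share of 30%, for example, would give up to 30%. The mentors' own change is reduced by the fraction e, whatever their share.

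**The case against.** The overlap is disclosed and reasoned. The intervention is aimed at the unit, mentors are its means of delivery, and colleagues are still untrained at baseline. That stands, and it limits the problem to the mentors. If training raises scores, the bias is also toward a smaller change, so it would not by itself produce a false positive answer to question 2.

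A reader might infer more than the documents support, in three ways:

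- *That mentors have no untrained baseline at all.* The three weeks are undated within an eight-month block, so some mentors may answer before their own training. What can be said is that an untrained baseline is not guaranteed.
- *That the mentors' gain is missing.* Only the part reached before the baseline answer is lost. Gain after that, up to 11/22-2/23, is still measured.
- *That the most trained group will show the least change.* The observed mentor change is g·(1 − e), against 1 for others. With g = 2 and e = 50% it is 2 × 0.5 = 1, the same as for others; with a smaller e it is larger. The protocol also specifies no comparison of change by amount of training.

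It can also be said that a separate analysis of mentors belongs in the SAP, which is not at hand, and that the staff background questionnaire (Appendix 1, not shown) may already record the mentor role. Both are fair. But no SAP can recover a pre-training measurement that was never scheduled, and that timing is set in the protocol.

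**Conclusion.** The point holds for the mentors, who are not assured an untrained baseline. Any gain they have before their baseline answer is lost from the question 2 change and from the staff mediators. The likely direction is understatement, provided that training raises the scores. The comparison for non-mentor staff is not affected.

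The size is not determinable from the protocol. With mentors at 5-15% of respondents, the pooled change is understated by 0-15% under equal gain and by at most about 26% if mentors gain twice as much. The lower end is zero because the documents allow every mentor to answer before training. The pooled effect may be small; the effect on the mentors' own change could be large. This is worth correcting because it is cheap, not because it invalidates the staff comparison.

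**What to change.** - Have each mentor complete the staff questionnaires (Appendices 1-4) before the first day of mentor training, and state this in the Data collection section and in Figure 2.
- Make mentor status identifiable in the staff data, if Appendix 1 does not already do so.
- Report the question 2 before-after change with and without mentors.
- If pre-training answers cannot be obtained, label the mentors' 2-4/21 scores as collected during mentor training and do not call them baseline.
- Apply the same flag to the daily FCC-provision answers only if these can be linked to a respondent. They are entered on a research computer in the unit through a questionnaire set up for each unit, and the protocol describes no individual identifier for them.

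Cost: mentors fill in the same forms some weeks earlier, and there is one extra analysis on a slightly smaller staff set. No new instrument is needed and the intervention is unchanged. Linking the daily answers, if wanted, could take more than a flag in the staff form.
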